## SYNCH trial

|               |                                                                                                                                     |
|---------------|-------------------------------------------------------------------------------------------------------------------------------------|
| Participants: | 18 – 75 years with fibrotic NASH (NAS $\geq 3$ , NASH F1-F3 $\geq 50\%$ , F0 $\leq 50\%$ )                                          |
| Arm 1:        | n = 24 receive vegan LFMT-capsules + A. soehngenii , B. animalis subsp. lactis and A. muciniphila       |
| Arm 2:        | n = 24 receive placebo-capsules (saline) + A. soehngenii , B. animalis subsp. lactis and A. muciniphila |

[figure not shown]

Figure 6: Study protocol

## 4. STUDY POPULATION

### 4.1 Population (base)

Recipient participants will be recruited from the multidisciplinary clinic for NAFLD-NASH Vascular Medicine/Hepatology by [name] (location AMC) and [name] (location VUmc, not part of the study staff) in Amsterdam UMC.

In order to forestall the influence of the dependent patient-physician relationship on the considerations of possible participants to enroll in the study, the following measures will be implemented. [name] is allowed to talk about the study with possible participants. In such a conversation, [name] shall point out that the patient is completely free to choose to either participate or refuse the study, and that his attitude towards the patient and the care that he provides will definitely not change as a result of the choice of the patient. In addition, we implemented a mandatory period of 7 days between the provision of information and the signing of the informed consent form.

Fecal donors will be healthy, lean (BMI 18 - 25 kg/m^2), male or female individuals on a stable (>3 months) plant-based vegan diet, with negative results for infectious diseases as recommended. Donors will be recruited by advertisements in the hospital, on social media and in local newspapers.

### 4.2 Inclusion criteria

#### *Patients*

- age 18-75 years
- biopsy-proven NASH obtained up to 32 weeks before screening: SAF Steatosis score  $\geq 1$ , Activity  $\geq 2$ , Fibrosis  $< 4$ ; 50% of participants should at least have NASH fibrosis stage 1, 2 or 3 according to the NASH CRN fibrosis staging system based on tandem reading of two expert liver pathologists
- fluency in Dutch or English
- participants should be able to understand the information and give informed consent

#### *FMT donors*

Donor feces will be collected from:

- Lean: BMI 18-25 kg/m^2

- Age 18 to 75 years
- No protonpump-inhibitor use or use of antibiotics in 3 months prior to donation
- Adherence to vegan diet

#### **4.3 Exclusion criteria**

A potential participant who meets any of the following criteria will be excluded from participation in this study:

##### *Patients*

- Current or history of significant alcohol consumption for a period of more than 3 consecutive months within 1 year before screening (significant alcohol consumption is defined as more than 2 international units/day for females and more than 3 international units/day for males, on average; 1 international unit contains  $\pm 14$  grams of alcohol)
- liver cirrhosis or hepatocellular carcinoma
- hepatitis B and/or C
- auto-immune hepatitis
- Wilson's disease
- primary sclerosing cholangitis
- primary biliary cholangitis
- alpha-1-antitripsine deficiency and hemochromatosis
- history of liver transplant, current placement on a liver transplant list
- use of pre-, pro- or synbiotics
- use of systemic antibiotics 3 month prior to randomization
- use of tamoxifen, methotrexate or amiodarone
- prior or planned bariatric surgery
- active GLP-1 receptor agonist treated diabetes mellitus
- bleeding disorder
- International normalized ratio (INR) of prothrombin time  $>1.4$  or platelet count  $<100 \times 10^9/L$  at screening
- anti-platelet/coagulant therapy use which cannot be temporarily discontinued
- any major cardiovascular event within 6 months prior to screening (e.g. myocardial infarction, cerebrovascular accident)
- prolonged compromised immunity (e.g. recent cytotoxic chemotherapy, HIV-infection with a CD4 count  $< 240$ )

- active or prior history of invasive malignancy (except for curatively treated in situ carcinomas [e.g., cervix] or non-melanoma skin cancer) unless a complete remission was achieved
- surgery scheduled for the trial duration period, except for minor surgical procedures, in the opinion of the investigator
- pregnant or nursing women
- any condition which, in the investigator's opinion, might jeopardize participants' safety or compliance with the protocol
- participation in another concomitant clinical trial.

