**Study population:**

Patients between age 18-75 years with biopsy-proven NASH obtained up to 32 weeks before screening based on tandem reading of two expert liver pathologists: SAF Steatosis score  $\geq 1$ , Activity  $\geq 2$ , Fibrosis  $< 4$ ; 50% of participants should at least have NASH fibrosis stage 1, 2 or 3 according to the NASH CRN fibrosis staging system.

Exclusion criteria are: Current or history of significant alcohol consumption for a period of more than 3 consecutive months within 1 year before screening (significant alcohol consumption is defined as more than 2 units/day for females and more than 3 international units/day for males, on average; 1 international unit contains  $\pm 14$  grams of alcohol), liver cirrhosis or hepatocellular carcinoma, hepatitis B and/or C, auto-immune hepatitis, Wilson's disease, primary sclerosing cholangitis, primary biliary cholangitis, alpha-1-antitripsine deficiency and hemochromatosis, history of liver transplant, current placement on a liver transplant list, use of pre-, pro- or synbiotics, use of systemic antibiotics 3 month prior to randomization, use of tamoxifen, methotrexate or amiodarone, prior or planned bariatric surgery, diabetes mellitus with active GLP-1 receptor agonist treatment, bleeding disorder, International normalized ratio (INR) of prothrombin time  $> 1.4$  or platelet count  $< 50 \times 10^9/L$  at screening, anti-platelet/coagulant therapy use which cannot be temporarily discontinued, any major cardiovascular event within 6 months prior to screening (e.g. myocardial infarction, cerebrovascular accident), prolonged compromised immunity (e.g. recent cytotoxic chemotherapy, HIV-infection with a CD4 count  $< 240$ ), active or prior history of invasive malignancy (except for curatively treated in situ carcinomas [e.g., cervix] or non-melanoma skin cancer) unless a complete remission was achieved, surgery scheduled for the trial duration period, except for minor surgical procedures in the opinion of the investigator, pregnant or nursing women, any condition which, in the investigator's opinion, might jeopardize participants' safety or compliance with the protocol, and participation in another concomitant clinical trial.

A total of 48 patients will receive synbiotic treatment with *A. soehngenii*, pasteurized *A. muciniphila*, *B. animalis* subsp. *lactis* and fructo-oligosaccharides, and will be randomized 1:1

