## Intervention:

### *Recipient participants*

From the first FMT until completion of the study, all recipient participants will receive an oral daily single dose of 5 g FOS. Subsequently, participants will be randomized to lean donor FMT capsules or placebo (blinded design). At baseline (day 0) and at week 8 (day 56) and week 16 (day 112) participants will ingest 21 LFMT or placebo capsules. In addition, participants will daily take 2 capsules of LFMT or placebo during the whole study period (24 weeks). The study visits will be 8 weeks apart, although a margin of -3 days to +3 days is implemented to take participants schedule and availability into account. We have previously observed that gut microbiota composition in the recipient is affected up to 8-12 weeks after donor FMT, so this time window ensures a stable donor gut microbiota composition during the study.

During the 24-week intervention period, all participants will take daily doses of  $10^9$  *A. soehngenii* CH-106 cells (dosage based on previous studies including toxicology study),  $10^{10}$  *B. animalis* subsp. *lactis* BLC1 (a well-studied strain marketed as a probiotic by Sacco SRL) and  $3 \times 10^{10}$  pasteurized *A. muciniphila* ATCC BAA-835T cells (dosage based on EFSA approval and obtained from A-Mansia Biotech).

Percutaneous liver biopsies will be performed as a part of screening when participants are theoretically eligible for participation, unless a liver biopsy has been performed in the previous 36 weeks. A tandem-read by two liver pathologists blinded to any other result will determine if patients will be included in the study. At 24 weeks, another liver biopsy will be performed to examine the effect of the FMT, which will also be reviewed by two liver pathologists (again blinded to any other result). The NASH-CRN classification will be assessed on H&E slides, for steatosis, inflammation and ballooning, and with a Sirius red–stained slide for evaluation of fibrosis. RNA for RNA-sequencing will be isolated. Differential gene expression will be assessed over time (baseline and 24 weeks) and by treatment allocation (vegan donor FMT versus placebo).

Feces will be collected at baseline, and after week 2, 8, 10, 16, 18, and 24, in order to investigate the changes in gut microbiome. Also, markers of gut barrier function will be assessed.

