## 3. STUDY DESIGN

### Study visits:

Participants who are foreseen to fulfil the inclusion / exclusion criteria for enrolment into the clinical study will be informed and interviewed. When theoretically eligible for participation, participants are asked to give informed consent in writing prior to any clinical study specific procedures. Both the participant and investigator (or designee) will sign and date the informed consent form. After, a liver biopsy will be performed (unless there is a liver biopsy available obtained < 32 weeks prior to screening) to assess if histopathological inclusion criteria are met.

A MRI of the liver and surrounding area (including pancreas and visceral adipose tissue; as previously specified) will be performed for all eligible participants before the biopsy, unless the biopsy was already performed prior to inclusion.

All eligible participants will visit the study physician 4 times; at baseline, after 8, 16, and 24 week. The study visits will be 8 weeks apart, although a margin of -3 days to +3 days is implemented to take participants schedule and availability into account.. At baseline, blood

and feces, will be collected, a Fibroscan will be made and participants will fill out the SF36.2 and CDLQ-NAFLD quality of life questionnaires. After, participants receive 21 LFMT or placebo capsules to orally ingest. The ingestion of the 21 capsules will be spread over the day to prevent clotting of capsules in the stomach. In addition, for the whole duration of the study participants will daily ingest 2 LFMT capsules (or placebo). At the next visit after 8 weeks blood will be withdrawn, feces will be collected and patients will again ingest 21 LFMT capsules (or placebo). The visit at 16 weeks will be the same as the visit at 8 weeks. The visit at 24 week will be the same as the baseline visit, however, at 24 weeks the visit will also include a liver biopsy. Moreover, patients will hand in fecal samples at baseline, week 2, 8, 10, 16, 18, and 24. Also, continuous glucose measurements will be performed at home using portable devices, during a consecutive period of 1 week (7 days) in the week before baseline, week 1, 9, 17 and 25.

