#### *Liver biopsy (after 24 weeks)*

At 24 weeks, another liver biopsy will be performed to examine the effect of the FMT. The NASH-CRN classification will be assessed on H&E slides, for steatosis, inflammation and ballooning, and with a Sirius red–stained slide for evaluation of fibrosis. RNA for RNA-sequencing will be isolated. Differential gene expression will be assessed over time (baseline and 24 weeks) and by treatment allocation (vegan donor FMT versus placebo).

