### 13. STRUCTURED RISK ANALYSIS

Also see the structured risk analysis performed for the SYNCH-study (enclosed).

The present study is considered an intermediate risk study. In summary, the two liver biopsies are the main contributors of risk for participants.

Liver biopsies know a complication rate of approximately 1:1000, with self-limiting bleeding as the main adverse event. We will use experienced personnel to reduce the chance of complications. To date, liver biopsy is still the golden standard in the assessment of progression or reduction of NASH, and there is no alternative. In therapy development for NASH, the American FDA, for example, demands liver biopsy in clinical trials. This study will, however, contribute to the further development and validation of multiparametric MRI as a substitute for biopsy by comparing the two.

To date, FMT procedures have not been associated with (serious) adverse events. Literature concerning the treatment with LFMT capsules reports a lower number of adverse events in comparison to the infusion of FMT via duodenal tube. The most prevalent side effects are mild, self-resolving abdominal pain, nausea, diarrhea, and flatulence (also see paragraph 6.4). Donors will be extensively screened for infectious diseases, rendering the chance of translocation of virulent actors small.

Fructo-oligosaccharides, in addition, are a subgroup of dietary fibers, which are already part of a varied diet. They are safe, well-researched and already over-the-counter available.

Moreover, *A. soehngenii*, *B. animalis*, *subsp. Lactis*, and *A. muciniphila* are commensals of the gut and all deemed safe to administer orally in toxicological studies and studies in humans, with no significant adverse event reported.

Last, we will withdraw blood (5x) and collect feces (7x), patients will complete several questionnaires and keep track of a food diary.

To evaluate and maximize the safety of participants, the study will be monitored by the clinical monitoring center and the DSMB.

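### The platelet exclusion limit is 50 × 10⁹/L in the Summary but 100 × 10⁹/L in section 4.3, and the accepted age of a prior biopsy is 32 weeks in three places and 36 weeks in two

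*Protocol*

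**What the plan says.** **Platelets.** The Summary, under Study population, excludes patients with INR above 1.4 "or platelet count $< 50 \times 10^9/L$ at screening". Section 4.3 (Patients) repeats the criterion with the same INR limit, but there it reads "or platelet count $<100 \times 10^9/L$ at screening". Section 4.3 opens its list with "A potential participant who meets any of the following criteria will be excluded from participation in this study".

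**Age of a prior biopsy.** Section 4.2 requires "biopsy-proven NASH obtained up to 32 weeks before screening", and the Summary (Study population) uses the same wording. Section 3 (Study visits) calls for a screening biopsy "unless there is a liver biopsy available obtained < 32 weeks prior to screening". The Summary (Intervention, Recipient participants) and section 8.3 (Screening liver biopsy) call for one "unless a liver biopsy has been performed in the previous 36 weeks" and give no date from which the 36 weeks are counted.

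**Why biopsies matter here.** Section 8.3 states: "At 24 weeks, another liver biopsy will be performed to examine the effect of the FMT". Section 13 says that "the two liver biopsies are the main contributors of risk for participants".

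**The concern.** These are thresholds on which staff act, and each has two current values.

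The platelet limit matters more. It is a bleeding safeguard for a percutaneous biopsy that every participant is due at week 24, and that many also have at screening. The Summary and section 11.3 both name bleeding at the biopsy site as the main complication. Someone screening from the Summary could enrol, and send for biopsy, a patient whom section 4.3 excludes.

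The biopsy window decides whether a patient undergoes an additional invasive procedure and whether an existing biopsy qualifies for entry. That biopsy also supplies the fibrosis score used for stratification (section 8.2) and the baseline for the histological primary outcome (section 8.1.2). Here the conflict lies within the body of the protocol, with sections 3 and 4.2 against section 8.3, so preferring the body over the Summary does not resolve it.

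**Working it through.** The protocol offers no calculation to reproduce on this point. The check sets every statement of each limit side by side.

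| Item | Place in the protocol | Limit |
|---|---|---|
| Platelets | Summary, Study population | excluded if < 50 × 10⁹/L at screening |
| Platelets | 4.3, Patients | excluded if < 100 × 10⁹/L at screening |
| Prior biopsy | Summary, Study population | up to 32 weeks before screening |
| Prior biopsy | 3, Study visits | < 32 weeks before screening |
| Prior biopsy | 4.2, Patients | up to 32 weeks before screening |
| Prior biopsy | Summary, Intervention | previous 36 weeks, no reference date |
| Prior biopsy | 8.3, Screening liver biopsy | previous 36 weeks, no reference date |

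**Platelets.** The two limits differ by a factor of 100 / 50 = 2. Counts below 50 are excluded under both and counts of 100 or more are allowed under both. Counts from 50 to 99 × 10⁹/L are allowed by the Summary and excluded by section 4.3. The time point is the same in both, so no reading satisfies both texts.

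**Biopsy age.** If screening is the reference date for both windows, the gap is 36 − 32 = 4 weeks. Take a biopsy 33 to 36 weeks old:

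- Under section 8.3 no new biopsy is ordered.
- Under section 3 a new biopsy is required.
- Under section 4.2 the old biopsy does not meet the inclusion criterion.

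If the 36 weeks ran to a later date such as baseline, the two windows would coincide when that date fell 36 − 32 = 4 weeks after screening. The text states no such date or interval, and both 36-week statements describe the biopsy as part of screening.

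**Superseded text?** Section 14.1 lists 9 changes and section 14.2 lists 7, so 9 + 7 = 16 entries. None concerns the platelet limit or the biopsy window. All seven statements in the table are current text.

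**Effect on the comparison.** Screening platelet count and the age of the qualifying biopsy are both fixed before randomisation. Neither conflict produces a systematic difference between the arms.

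**The case against.** The strongest reply is that the practical effect is small. Section 4.3 is the formal list, it carries the stricter platelet limit, and a site that follows it exposes nobody to added risk. Other safeguards also apply to a patient with 50 to 99 × 10⁹/L: the exclusions for cirrhosis, bleeding disorder and INR above 1.4, the investigator's discretion to exclude on safety grounds, and ultrasound-guided biopsy by an experienced radiologist. Nothing shows that even one of the 48 participants would fall in the disputed range. For the biopsy window, section 4.2 controls entry whatever section 8.3 waives, the gap is at most 4 weeks, and an unstated later reference date might reconcile the figures.

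Most of this stands, and it limits the finding. The platelet exposure is confined to someone working from the Summary, and the biopsy conflict leads mainly to queries, repeat biopsies or eligibility deviations. It does not remove the contradictions. The protocol has no rule saying which section prevails; treating section 4.3 as operative follows from its role as the formal list and is not a written provision. The reconciling reference date is also absent from the text.

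Two smaller objections are fair but change nothing. The Summary's burden text describes the anticoagulant exclusion more loosely than the criteria lists, although the lists themselves agree. The difference between less than 32 weeks (section 3) and up to 32 weeks (section 4.2) affects only a biopsy exactly 32 weeks old.

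**Conclusion.** Both contradictions are real and stand in current text. The point should be fixed, mainly because of the platelet limit, a bleeding safeguard for the procedure that the protocol itself ranks as its main risk.

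Patients with 50 to 99 × 10⁹/L are classified in opposite ways; their number cannot be derived from the document. The biopsy conflict adds at most 4 weeks to the age of the baseline histology, assuming that both windows are counted from screening. It is the lesser of the two. Neither affects the sample size or the planned analysis.

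**What to change.** - **Summary, Study population:** change the platelet limit to below 100 × 10⁹/L, matching section 4.3, unless the responsible clinicians justify another single value for both places.
- **Summary, Intervention, and section 8.3, Screening liver biopsy:** replace the 36-week waiver with a biopsy obtained in the 32 weeks before screening, matching sections 3 and 4.2. If 36 weeks was what the investigators intended, they should say so, name the reference date and change the 32-week statements instead.
- **Optional, in the same amendment:** use one form of words for the 32-week boundary in section 3 and section 4.2.

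The cost is 1 + 2 = 3 wording edits in an amendment, plus the optional one. If screening has begun, the screening log should also be checked for platelet counts of 50 to 99 × 10⁹/L and for qualifying biopsies more than 32 weeks old at screening. Any enrolled patient with such a platelet count should be reviewed before the week-24 biopsy.

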#### *FMT donors*

FMT donors with one of the following will be excluded, screening will be performed at the first visit, once after 1-2 months, and thereafter every 3 months (as recommended by 'fecal transplantation guidelines'). The screening will be executed following a step by step approach. First, potential donors will receive the information letter. The informed consent will be executed via telephone, whereafter potential donors sign the informed consent forms and send via mail to the researcher. When potential donors are eligible and informed consent is obtained, potential donors will receive a questionnaire. Depending on eligibility as assessed with the questionnaire, potential donors will be screened for parasites using a double feces test (DFT). When potential donors pass this screening, the rest of the screening, consisting of further fecal analysis and a blood withdrawal, will be completed. In addition, not for screening ends, but for investigational purposes (to assess the composition of donors gut microbiome), the last step of the screening of the potential donors will also include a 16s-sequencing to analyse the gut microbiome of potential donors. The parameters that the screening include are:

- Unsafe sex practice and other factors that imply a high risk of acquiring infectious diseases (questionnaire)
- Any medication use including PPI and antibiotics in the past 3 months
- Serological presence HIV, hepatitis A, B and/or C, active cytomegalovirus (CMV), active Epstein-Barr virus (EBV), lues, amoebiasis or strongyloides
- Presence of fecal bacterial pathogens (Salmonella, Shigella, Campylobacter, Yersinia, enteropathogenic E. coli), transmittable viruses (Rotavirus, Norovirus, enterovirus, parechovirus, sapovirus, adenovirus 40/41/52, astrovirus), parasites, multidrug resistant bacteria (MDR), extended spectrum beta-lactamase producing bacteria (ESBL).

- Positive *C. difficile* stool test
- Individuals with an increased risk for one of the above conditions (e.g. high-risk sexual contacts, recent blood transfusions) will be excluded.

